| PRIMARY OBJECTIVE     | Determine the changes of central corneal sensitivity, Schirmer I test (SIT), noninvasive tear breakup time (NI-TBUT), tear meniscus height, corneal fluorescein (FL) staining, ocular surface disease index (OSDI) and tear concentrations of interleukin-1 $\alpha$ (IL-1 $\alpha$ ), tumor necrosis factor- $\alpha$ (TNF- $\alpha$ ), nerve growth factor (NGF), interferon- $\gamma$ (IFN- $\gamma$ ), transforming growth factor- $\beta$ 1 (TGF- $\beta$ 1) and matrix metalloproteinase-9 (MMP-9) of the two surgeries preoperatively and postoperatively.                                                                                                                                                                                                                                                                                                                                                                                                                                                                                                                                                                                                                                                                                                                                                                                                     |

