| DURATION OF SUBJECT PARTICIPATION AND DURATION OF STUDY | 
Subjects will be on study for up to 2 months
 
Screening: 2-4weeks
 
Treatment: 1day
 
Follow-up: 1day, 1week and1month (1 month in total)
 
The total duration of the study is expected to be 9 months.
                                                                                                                                                                                                                                                                                                                                                                                                                                                                                                                                                                          |
| STATISTICS PLAN                                         | 
Data were analyzed using SPSS 19.0 software (SPSS, Chicago, IL, USA). Paired samples t-test (normally distributed data) or Wilcoxon test (non-normally distributed data) was used to determine significant differences between pre- and post-operative measurements in each group. Comparisons between the two groups were performed by Independent samples t-test (normally distributed data) or Mann-Whitney U test (non-normally distributed data). Pearson or Spearman rank correlation was used to analyzed for the correlations between tear inflammatory mediators and ocular surface parameters. P value of less than 0.05 was considered statistically significant. Data are presented as mean <math>\pm</math> SD.
                                                                   |

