## **2 STUDY RATIONALE**

This first all-in-one FS-laser system was designed to perform the refractive lenticule extraction (ReLEx) procedures, femtosecond lenticule extraction (FLEx) and small-incision lenticule extraction (SMILE). In FLEx, a corneal flap is created by the FS laser (similar to LASIK) and lifted, allowing lenticule removal[1-3]. For SMILE, a truly flapless procedure, only a small—2-4mm—incision is made, through which the lenticule is removed. Multiple etiologies contribute to this ocular surface disruption, including the flap creation and stromal ablation involved in previous refractive surgery techniques, such as: disable tear film, damage of the corneal nerve and postoperative inflammatory mediator. For both FLEx and SMILE, stromal ablation has been replaced by refractive lenticule removal. In terms of corneal flap formation, FLEx still requires an epithelial-stromal flap, while SMILE employs only a small incision to extract the lenticule. Hence, we hypothesize that SMILE will have less effect on patients' ocular surface markers and inflammatory mediators, compared to FLEx. To test our hypothesis, we conducted a prospective clinical study in patients who underwent FLEx or SMILE. Ocular surface parameters and inflammatory mediators were assessed and compared between the different types of surgery.

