## **3 STUDY OBJECTIVES**

### **3.1 Primary Objective**

3.1.1.Determine the changes of ocular surface including central corneal sensitivity, Schirmer I test (SIT), noninvasive tear breakup time (NI-TBUT), tear meniscus height, corneal fluorescein (FL) staining, ocular surface disease index (OSDI) of the two surgeries preoperatively and postoperatively

3.1.2.Evaluation the changes of tear concentrations of interleukin- $1\alpha$  (IL- $1\alpha$ ), tumor necrosis factor- $\alpha$  (TNF- $\alpha$ ), nerve growth factor (NGF), interferon- $\gamma$  (IFN- $\gamma$ ), transforming growth factor- $\beta 1$  (TGF- $\beta 1$ ) and matrix metalloproteinase-9 (MMP-9) of the two surgeries preoperatively and postoperatively.

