## **4 STUDY DESIGN**

This is a single center, prospective and non-randomly study. 41 patients are planned to be enrolled. They are divided into two groups. One group will undergo the FLEx surgery, the other group will undergo the SMILE surgery. The ocular surface parameters and concentration of tear inflammatory mediators will be assessed at baseline, 1 day,1 week and 1 month postoperatively. Subjects who meet all inclusion criteria and none of the exclusion criteria will be entered into the study.

1. Minimum age of 18 years(range from 18 year to 25 years).
2. Corneal thickness more than 500  $\mu\text{m}$  and calculated residual stromal bed after treatment greater than 300  $\mu\text{m}$ .
3. Corneal thickness more than 500  $\mu\text{m}$  and calculated residual stromal bed after treatment greater than 300  $\mu\text{m}$ .
4. Preoperative cylindrical equivalent refraction between -0.25 D and -1.50 D.
5. Preoperative corneal curvature from 41.0 D to 46.0 D with a regular topographic pattern.

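### Twelve primary measures have no lead outcome, lead visit or success rule, and every comparison is judged at an unadjusted P<0.05, so the false-positive chance of the between-operation conclusion is above the nominal level

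*Protocol*

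**What the plan says.** **Outcomes.** Protocol section 3.1 has two parts. The first begins "Determine the changes of ocular surface including central corneal sensitivity, Schirmer I test (SIT), noninvasive tear breakup time (NI-TBUT), tear meniscus height" and goes on to fluorescein staining and OSDI. The second begins "Evaluation the changes of tear concentrations of" and names six mediators: IL-1α, TNF-α, NGF, IFN-γ, TGF-β1 and MMP-9. The synopsis puts the same twelve under one primary objective. Neither place ranks them or says which results would count as success.

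**Hypothesis.** Section 2 states one directional hypothesis, that SMILE disturbs the ocular surface markers and mediators less than FLEx, and says that the study was run to test it: "Ocular surface parameters and inflammatory mediators were assessed and compared between the different types of surgery".

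**Visits.** Section 4: "The ocular surface parameters and concentration of tear inflammatory mediators will be assessed at baseline, 1 day,1 week and 1 month postoperatively". Sections 7.3.1 and 7.3.3 drop day 1 for corneal sensitivity and for staining. Sections 7.3.2 and 7.3.4 to 7.3.6 keep all three post-operative visits for the other four clinical measures.

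**Tests.** From the synopsis Statistics Plan: "Comparisons between the two groups were performed by Independent samples t-test (normally distributed data) or Mann-Whitney U test". For changes from baseline, a paired t-test or Wilcoxon test "was used to determine significant differences between pre- and post-operative measurements in each group". A single threshold applies throughout: a P "value of less than 0.05 was considered statistically significant". No lead visit, testing order or multiplicity adjustment is given.

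**The concern.** The study puts forward one conclusion, about which operation disturbs the eye less, but gives many routes to it. Each named two-sample test takes one outcome at one time, and no repeated-measures model or summary measure is specified. The natural reading is therefore one test per outcome per visit, each at 0.05.

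With no lead outcome, lead visit or success rule, nothing in the protocol prevents any single significant result from being read as support. The 0.05 is then the error rate of one test and not of the conclusion. What is at stake is whether a reported advantage of one operation, picked from twelve measures and up to three visits, can be told apart from chance.

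**Working it through.** **The plan's own figures.** The protocol states no family-wise error rate to reproduce. The total of 41 comes without effect size, SD, power or arm sizes, so it cannot be rebuilt either.

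**Inputs.**
- Threshold 0.05 (Statistics Plan). Sidedness is not stated; two-sided is assumed.
- Twelve outcomes (section 3.1).
- Post-operative visits: 2 for corneal sensitivity and staining, 3 for the other four clinical measures (section 7.3), and 3 for the mediators (section 4).
- Correlations between test statistics: none given, so a range is assumed.
- Arm sizes: not given; 20/21 is assumed for the power figures only.

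**Step 1, number of between-group tests.** 2 + 2 + 4×3 + 6×3 = 34. A plain 12×3 = 36 would overcount, because two measures skip day 1.

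**Step 2, independent tests, no true difference.** Chance of at least one P<0.05 = 1 − 0.95^34 = 0.825. Expected false positives = 34 × 0.05 = 1.7, whatever the correlation.

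**Step 3, correlated tests.** For jointly normal statistics with common correlation ρ and c = 1.96, the chance is

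1 − ∫ φ(u) [Φ((c − √ρ·u)/√(1−ρ)) − Φ((−c − √ρ·u)/√(1−ρ))]^34 du.

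**Step 4, only results favouring SMILE.** The stated hypothesis is directional, so a significant result favouring FLEx would not support it. Each test then contributes 0.025. Under independence the chance is 1 − 0.975^34 = 0.577; otherwise drop the second Φ term in step 3.

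| Assumed common correlation | Any difference (nominal 5%) | Favouring SMILE only (nominal 2.5%) |
|---|---|---|
| 0 | 82.5% | 57.7% |
| 0.3 | 69.9% | 37.3% |
| 0.5 | 53.5% | 26.9% |
| 0.7 | 35.4% | 17.7% |
| 0.9 | 17.7% | 8.9% |

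**Step 5, a more structured correlation.** A simulation of 34 pooled t-tests (20 v 21 patients, 10,000 runs per setting) used separate correlations across visits within an outcome and between outcomes at one visit. The chance of any difference was 79% at 0.5/0, 73% at 0.5/0.3, 57% at 0.7/0.5 and 29% at 0.9/0.8.

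**Step 6, one visit only.** With all 12 outcomes at a single visit, still unadjusted, the chance is 1 − 0.95^12 = 46% if independent and 32% at correlation 0.5. Fixing the visit alone does not solve the problem.

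**Step 7, cost of adjusting.** Two-sample t-test, 20/21, 80% power, noncentral t: 0.90 SD at 0.05; 1.21 SD at 0.05/11; 1.22 SD at 0.05/12. The last two are the strictest Holm step, so they are upper bounds.

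**The case against.** **The large figures depend on assumptions.** A reader might infer that a false difference is very likely. The documents do not support that as it stands. The same eye is measured repeatedly within a month, and all six mediators come from one tear sample and one array, so independence is doubtful. At high correlation the chance falls to 35% or 18%. Counting only results favouring SMILE lowers it further. This objection stands as to size. It does not bring any case down to the nominal level, and uniformly high correlation across a questionnaire, a filament test, a paper strip and six proteins is hard to believe.

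**The measures are not co-primary.** A reader might call them so. In strict usage that means all must succeed, which would not inflate the error. The protocol sets no success rule of either kind, so the inflation holds if one significant result is taken as enough. That condition is an inference, though nothing in the text excludes it.

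**Visit-by-visit testing is implied.** The Statistics Plan does not say at which visits, or on raw values or changes, the groups are compared. The count of 34 is the natural reading, not a stated number. The paired within-group tests, 2 × 34 = 68, do not bear on whether the operations differ and are left out.

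**An SAP may deal with it, and the study is small and mechanistic.** Multiplicity detail often does sit in an SAP, and the non-random allocation also limits any between-operation conclusion. But this protocol carries its own Statistics Plan, fixes the flat threshold there, states a hypothesis to be tested, and nowhere calls itself exploratory. The point therefore rests on what is written.

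**Conclusion.** The point holds. Followed as written, the plan lets one between-operation conclusion rest on any of 34 unadjusted comparisons. The false-positive chance runs from 82.5% under independence to about 18% at a common correlation of 0.9. Counting only results favouring SMILE, it runs from about 58% to about 9%, against a nominal 2.5%.

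These figures assume two-sided tests, one test per outcome per visit, no true difference on any measure, and that one significant result is read as a difference. Since the protocol gives no correlations, the range should be quoted and not the top figure alone.

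A reader might also infer that corneal sensitivity at 1 month is the obvious lead outcome, because section 1 calls nerve damage the main cause of dry eye. The documents do not settle this. The same section also calls mediator fluctuations a key factor, half the hypothesis concerns mediators, and the title speaks of early changes.

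**What to change.** In section 3.1 and the Statistics Plan, the investigators should do one of the following, before any comparative data are looked at:

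- **Preferred:** name one primary outcome at one visit, tested at two-sided 0.05. Make the other outcomes secondary, with Holm across the 11 at that visit, and state that the conclusion rests on the primary.
- **If all 12 stay primary:** name one visit and apply Holm across the 12 there.

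Corneal sensitivity and staining are not measured on day 1, so a family containing both needs 1 week or 1 month as its visit. The choice of outcome and visit is the investigators'. In either case, report the other visits and the within-group comparisons as estimates with confidence intervals and label them descriptive.

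The change is to wording only and needs no extra patients, visits or assays. The price is power on adjusted outcomes: from 0.90 SD at 0.05 to at most about 1.21 SD (11 secondaries) or 1.22 SD (12 primaries), with an assumed 20/21 split and 80% power. A single named primary keeps the full 0.05.

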## **1 BACKGROUND**

The use of femtosecond (FS) laser has become one of the most significant technological advancements in refractive surgery. A breakthrough FS laser-assisted myopic and myopic astigmatic correction procedure can now be performed using a prototype of the VisuMax femtosecond system. This first all-in-one FS-laser system was designed to perform the refractive lenticule extraction (ReLEx) procedures, femtosecond lenticule extraction (FLEx) and small-incision lenticule extraction (SMILE). In FLEx, a corneal flap is created by the FS laser (similar to LASIK) and lifted, allowing lenticule removal. For SMILE, a truly flapless procedure, only a small—2-4mm—incision is made, through which the lenticule is removed.

Ocular surface disruption during corneal refractive surgery is commonly considered to be closely related to the development of dry eye. Multiple etiologies contribute to this ocular surface disruption, including the flap creation and stromal ablation involved in previous refractive surgery techniques. Corneal nerve damage has been considered the main cause of dry eye, due to disrupted afferent sensory nerves, reduced blink reflex, and increased tear evaporation leading to tear film instability. In addition, postoperative inflammatory mediator fluctuations are also a key factor related to ocular surface damage. Extensive research has described the effects of cytokines, chemokines and growth factors in modulating corneal wound healing, cell migration, and apoptosis on the ocular surface after refractive surgery.

## **2 STUDY RATIONALE**

This first all-in-one FS-laser system was designed to perform the refractive lenticule extraction (ReLEx) procedures, femtosecond lenticule extraction (FLEx) and small-incision lenticule extraction (SMILE). In FLEx, a corneal flap is created by the FS laser (similar to LASIK) and lifted, allowing lenticule removal[1-3]. For SMILE, a truly flapless procedure, only a small—2-4mm—incision is made, through which the lenticule is removed. Multiple etiologies contribute to this ocular surface disruption, including the flap creation and stromal ablation involved in previous refractive surgery techniques, such as: disable tear film, damage of the corneal nerve and postoperative inflammatory mediator. For both FLEx and SMILE, stromal ablation has been replaced by refractive lenticule removal. In terms of corneal flap formation, FLEx still requires an epithelial-stromal flap, while SMILE employs only a small incision to extract the lenticule. Hence, we hypothesize that SMILE will have less effect on patients' ocular surface markers and inflammatory mediators, compared to FLEx. To test our hypothesis, we conducted a prospective clinical study in patients who underwent FLEx or SMILE. Ocular surface parameters and inflammatory mediators were assessed and compared between the different types of surgery.

### **2.1 Risk/Benefit Assessment**

There are no adverse events reported in the literature do date. The risks associated with the research is indicated as following:

### **2.1.1 Risk of dry eye**

The patients may experience dry eye after the refractive surgery. We will exclude the patients who already have dry eye in order to avoid more potential sever dry eye syndrome postoperatively.

### **2.1.2 Risk of overcorrections or undercorrections**

We will make a appropriate surgery strategy according to patients' refractive status, best corrected visual acuity and demands.

### **2.1.3 Risk of vision returning**

The risk of vision returning for patients with high myopia may be higher than patients with medium and low myopia after surgery

## **3 STUDY OBJECTIVES**

### **3.1 Primary Objective**

3.1.1.Determine the changes of ocular surface including central corneal sensitivity, Schirmer I test (SIT), noninvasive tear breakup time (NI-TBUT), tear meniscus height, corneal fluorescein (FL) staining, ocular surface disease index (OSDI) of the two surgeries preoperatively and postoperatively

3.1.2.Evaluation the changes of tear concentrations of interleukin- $1\alpha$  (IL- $1\alpha$ ), tumor necrosis factor- $\alpha$  (TNF- $\alpha$ ), nerve growth factor (NGF), interferon- $\gamma$  (IFN- $\gamma$ ), transforming growth factor- $\beta 1$  (TGF- $\beta 1$ ) and matrix metalloproteinase-9 (MMP-9) of the two surgeries preoperatively and postoperatively.

### **3.2 Secondary Objective**

Determine the correlation between inflammatory mediators and ocular surface changes.

## **4 STUDY DESIGN**

This is a single center, prospective and non-randomly study. 41 patients are planned to be enrolled. They are divided into two groups. One group will undergo the FLEx surgery, the other group will undergo the SMILE surgery. The ocular surface parameters and concentration of tear inflammatory mediators will be assessed at baseline, 1 day,1 week and 1 month postoperatively. Subjects who meet all inclusion criteria and none of the exclusion criteria will be entered into the study.

1. Minimum age of 18 years(range from 18 year to 25 years).
2. Corneal thickness more than 500  $\mu\text{m}$  and calculated residual stromal bed after treatment greater than 300  $\mu\text{m}$ .
3. Corneal thickness more than 500  $\mu\text{m}$  and calculated residual stromal bed after treatment greater than 300  $\mu\text{m}$ .
4. Preoperative cylindrical equivalent refraction between -0.25 D and -1.50 D.
5. Preoperative corneal curvature from 41.0 D to 46.0 D with a regular topographic pattern.

## **5 SUBJECT SELECTION**

### **5.1 Study Population**

Subjects with a diagnosis of myopia and/or astigmatism who meet the inclusion and exclusion criteria will be qualified to participate in this study.

### **5.2 Inclusion Criteria**

1. Minimum age of 18 years(range from 18 year to 25 years).
2. Corneal thickness more than 500  $\mu\text{m}$  and calculated residual stromal bed after treatment greater than 300  $\mu\text{m}$ .
3. Corneal thickness more than 500  $\mu\text{m}$  and calculated residual stromal bed after treatment greater than 300  $\mu\text{m}$ .
4. Preoperative cylindrical equivalent refraction between -0.25 D and -1.50 D.
5. Preoperative corneal curvature from 41.0 D to 46.0 D with a regular topographic pattern.

### **5.3 Exclusion Criteria**

1. Systemic disease that contraindicated the surgery (such as diabetes, glaucoma and systemic collagen vascular disease).
2. Corneal abnormality or disease.
3. A history of tear supplement usage.
4. A history of contact lens wear during the past year.

## **6 CONCURRENT MEDICATIONS**

Standard postoperative treatment consisted of 0.3% tobramycin/dexamethasone (TobraDex, Alcon) eyedrops, 0.5% levofloxacin (Cravit, Santen) eyedrops and sodium hyaluronate (HYCOSAN, URSAPHARM Arzneimittel GmbH) four times a day for one week. Tobradex and Cravit were suspended after one week, but artificial tear eyedrops were applied as required until one month.

## **7 STUDY PROCEDURES AND GUIDELINES**

All patients provided written consent to participate in the study and finished all postoperative follow-up visits. All surgeries were performed by the same experienced surgeon ([name]) following standard procedures under topical anesthesia. One eye of each subject was selected randomly for statistical analysis.

### **7.1 Surgery Procedure**

#### **7.1.1 FLEx**

The VisuMax femtosecond laser system (Carl Zeiss Meditec AG, Jena, Germany) with a 500 kHz repetition rate will be used to perform FLEx surgery. Four femtosecond incisions will be created in succession: the posterior surface of the refractive lenticule (spiral in), the lenticule border, the anterior surface of the refractive lenticule (spiral out), and the corneal flap in the superior region. After the suction is released, the flap is opened using a thin, blunt spatula and the free refractive lenticule is subsequently grasped with a forceps and extracted, after which the flap is repositioned carefully.

The planned flap thickness with superior hinge and 50 degrees in cordal length is 120  $\mu\text{m}$ . The flap diameter is 7.5  $\mu\text{m}$  and the lenticule diameter 6.5 mm. The optical zone size is 6.5  $\mu\text{m}$ . The spot spacing and tracking spacing is 4.5  $\mu\text{m}$  for the lenticule and 2.0  $\mu\text{m}$  for the lenticule side cut. The energy of the femtosecond laser is 140nJ.

#### **7.1.2 SMILE**

ReLEx SMILE surgery will be also performed using the Visu Max femtosecond laser system with a 500 kHz repetition rate. The only difference from the ReLEx FLEx procedure is to make a small incision in the last step, instead of creating a corneal flap. Once the four incisions is created, suction is released automatically and the anterior and posterior refractive surfaces are separated by a thin, blunt spatula. The refractive lenticule is extracted through the incision using forceps.

The optical zone size was 6.5 mm. The anterior lenticule surface was 120 µm deep. The small incision was located in the 120° position, with 50 µm cordal length (the side-cut incision with a circumferential length of 4.0–5.0 mm and angle of 90 °). The spot spacing and tracking spacing is 4.5 mm for the lenticule, 2.0 mm for the lenticule side cut, 3.0 mm for the small incision and 2.0 mm for the small incision side cut. The energy of the femtosecond laser is also 140nJ.

